**Participants flow chart**

Following the CONSORT guidelines (21), a flow chart will be drawn describing the situation during the course of the trial of all invited patients, including the number of those who refused to participate before randomization, the assignment to each treatment arm, losses to follow-up and possible crossovers.

**Intervention**

Patients who agree to participate in the study will be randomly assigned to one of the two intervention groups. The assignment will be made by a computer-generated list (SPSS 19 program), balancing the participants between the groups according to the degree of baseline disability at study entry, and the randomization being supervised by a statistician outside the research team. The randomization sequence will be concealed.

The NMV group will receive treatment with 5 cm wide NMV, applied according to the clinical examination, based on the following guideline: If the lumbar pain in flexion or extension improves a) when mobilizing the skin / fascia longitudinally to the paravertebral musculature, the muscular technique will be applied, with the base positioned in the sliding direction, without tension and in a position of maximum lumbar flexion possible, b) when mobilizing the skin / fasciae in approximation towards a point, the technique of space (or ligament), with approximately 75% tension and in a position of maximum possible lumbar flexion, c) when mobilizing the skin / fasciae transversely to the paravertebral musculature, the fascia technique will be applied, in a position of maximum flexion lumbar possible (several techniques can be combined, depending on the examination).

In the placebo group, the same bandage will be applied but in a neutral body position, without tension and applied transversely at a vertebral level that is not painful on palpation (12).

The duration of treatment will be 4 weeks, changing the bandage 4 times, weekly.

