**OBJECTIVES**

- Main objective: To evaluate the short and medium term efficacy of NMV treatment in pain, disability and quality of life in patients with CMLBP, through a controlled and randomized study.

- Secondary objectives: 1) To evaluate the effect of NMV treatment on the muscle activity patterns of the trunk, abdominal and hamstring extensors obtained by electromyography with surface electrodes. 2) To analyze the influence of fear-avoidance beliefs, of catastrophizing ideas, of the presence of anxiety-depression, and of pain-coping strategies on the effectiveness of the VNM in the treatment of patients with CMLBP.

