**Outcome measures**:

The following variables will be taken into account in the clinical trial:

- Sociodemographic data: age, sex, profession (classification according to CNAE), sedentary lifestyle (sedentary, sedentary with walking, light or intense physical effort), sporting activity (no sport, low-impact sport, high-impact sport; weekly frequency).

- Clinical variables: weight and height (BMI), process evolution time (in months), previous pharmacological treatment (type, dose, duration), previous physical treatment (type, duration), complementary examinations (Rx, CT, MRI)

- Evaluation of results:

Currently, there is consensus regarding the basic variables to be considered in the evaluation of results in the treatment of low back pain: pain, specific functional limitation due to low back pain, quality of life, work disability and satisfaction (22,23,24). Based on these consensuses, in the evaluation of results we will take into account the following variables:

- Pain intensity: Numerical Pain Scale (NPS), preferable to the visual analog scale because it is less abstract and easier to understand (24).
- Study of SEMG of lumbar spinal erectors, oblique / transverse abdominals, and hamstrings. The muscle activation pattern will be studied descriptively, checking the presence or absence of relaxation in maximum flexion. The pre and post-treatment patterns will be compared again, checking the existence or not of relaxation, and using averages and ratios of electromyographic activity.

• Limitations of the activity: validated version in Spanish of the Roland-Morris Questionnaire (RMQ), useful in situations of mild and moderate disability, more typical of the population usually attended in the MFyRHB consultations (25,26,27,28).

• Quality of life: validated Spanish version of the SF-36 questionnaire (29).

• Work situation: active in their usual job, active in a restricted job, Temporary Disability, Permanent Disability, unemployed due to health problems, unemployed for other reasons, student, housewife, retired (22).

• Fear-avoidance beliefs: validated Spanish version of the Fear Avoidance Beliefs Questionnaire (FABQ) (30,31) that measures beliefs and attitudes regarding the potential effect of work and physical activity on pain.

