Descriptive statistics will be obtained by expressing continuous variables as mean (standard deviation) or median (quartiles) according to their normality or not, categorical variables in number (percentage) and expressing in all cases the 95% confidence interval. The normal distribution will be verified by the Kolmogorov test to determine the use of parametric or non-parametric tests. For comparison of continuous variables between groups, the Student's t tests or the Mann-Whitney U tests will be used and for categorical variables the Chi-square or Fisher's test according to the type of distribution. Intragroup changes in continuous variables at the end of treatment and at 6 months will be analyzed with Student's t test for paired samples. To assess whether there are differences between the two groups in pain, disability and in the different variables, analysis of covariance (ANCOVA) will be performed, one for each dependent variable. In all the tests, the independent variable will be the group while the covariate variable will be the baseline level of each dependent variable. It will be necessary to have comparable levels in both groups to correctly interpret the ANCOVA results. Therefore, several Student's t tests will be performed, one for each dependent variable, considering each group as an independent variable in each case. To assess whether the changes in the 2 groups occur differently, several ANOVAs will be performed, one analysis for each dependent variable. In all cases, the independent variable will be the group and the time in which the data are collected. In this analysis, only the possible presence of interactions is studied. In addition, the correlations between the study variables will be evaluated using Pearson's r or Spearmann's Rho according to normality. Two models of multiple linear regression will also be applied with pain and disability as dependent variables and in both models age, sex, pain, catastrophization, fear-avoidance, sick leave, evolution time and anxiety-depression as independent variables.

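### Allocation is balanced on baseline disability, but the fixed ANCOVA covariate rule leaves that factor out of the pain and SF-36 models: mildly conservative tests and some lost precision, not bias

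*Protocol*

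**What the plan says.** **Allocation.** The Intervention section describes a computer-generated list "balancing the participants between the groups according to the degree of baseline disability at study entry". It does not name the instrument, the cut-offs or the balancing method.

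**Between-group model.** Under Data collection and analysis, "analysis of covariance (ANCOVA) will be performed, one for each dependent variable". The adjustment is then set for all of them: "In all the tests, the independent variable will be the group while the covariate variable will be the baseline level of each dependent variable".

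**Other analyses in the same section.** For the group-by-time ANOVAs, "In all cases, the independent variable will be the group and the time in which the data are collected". The t, Mann-Whitney, chi-square and Fisher comparisons are unadjusted. The two multiple regressions for pain and disability use, "in both models age, sex, pain, catastrophization, fear-avoidance, sick leave, evolution time and anxiety-depression as independent variables"; baseline disability is not listed, and neither is treatment group, so they are not treatment comparisons.

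**Main objective.** "To evaluate the short and medium term efficacy of NMV treatment in pain, disability and quality of life in patients with CMLBP". Pain and quality of life therefore stand beside disability, which is measured by the RMQ.

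**The concern.** When allocation is forced to balance a factor that predicts the outcome, the treatment estimate varies less from trial to trial than under simple randomisation. A model without that factor does not know this. It leaves the variation due to the factor in the residual and reports a standard error that is somewhat too large. Intervals are then too wide and tests reject too seldom under the null. Separately, the model gives up the ordinary precision gain from a prognostic covariate.

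The covariate rule covers the balancing factor only where the outcome is disability itself. Pain and SF-36 are main-objective outcomes in a small trial, and the sample size was derived for RMQ alone, so precision on these two has no planned margin. The section states a positive rule for every test. An analysis plan that followed it would carry the mismatch forward, so this is not a detail left for later.

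**Working it through.** **1. The plan's own figure.** Inputs from Power and sample size: difference 3 RMQ points, SD 3.2, two-sided alpha 0.05, power 0.90 (reading the stated beta of 0.9 as power).

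n per group = 2(1.96 + 1.282)² × 3.2² / 3² = 2 × 10.51 × 10.24 / 9 ≈ 23.9, so 24. This reproduces. With 20% losses, 24 / 0.8 = 30 per group, or 60 in total, against the stated 62. The checks below use N = 48 analysed.

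**2. Where the balancing factor appears.**

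| Analysis | Terms stated | Baseline disability included? |
|---|---|---|
| ANCOVA, disability | group, own baseline | yes, if allocation used RMQ |
| ANCOVA, pain | group, baseline pain | no |
| ANCOVA, SF-36 | group, baseline SF-36 | no |
| Group-by-time ANOVAs | group, time | no, except as the first RMQ measurement |
| t, Mann-Whitney, chi-square, Fisher | group | no |

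**3. Limiting case.** Let r be the partial correlation between baseline RMQ and the outcome given the outcome's own baseline. No such figure is in the protocol; 0.2, 0.3 and 0.5 are assumptions. If allocation removed all imbalance in disability:

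- Reported over true standard error = 1/√(1 − r²) = 1.021 / 1.048 / 1.155.
- Type I error = 2[1 − Φ(1.96/√(1 − r²))] = 0.045 / 0.040 / 0.024.

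These are bounds. Balancing on two or three categories leaves imbalance within them.

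**4. Simulation under stratified allocation.** N = 48, two or three strata of baseline disability, correlation 0.3–0.5 between the outcome's own baseline and baseline disability.

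| Assumed r | Type I error, own baseline only | Reported SE above true SE | SE narrowing when disability is added | Power gain at 0.8 SD |
|---|---|---|---|---|
| 0.2 | 0.045–0.049 | 0–2% | about 2% | about 1 point |
| 0.3 | 0.042–0.049 | 1–3% | about 4% | about 3 points |
| 0.5 | 0.026–0.034 | 5–11% | about 13% | about 9 points |

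The narrowing agrees with 1 − √(1 − r²) = 2.0% / 4.6% / 13.4%, less a little for the extra parameter. Further runs with correlations up to 0.7 (5,000 per setting, Monte Carlo error about 0.003) gave type I error of 0.046–0.053 / 0.042–0.049 / 0.031–0.040. The r = 0.5 value is therefore best read as roughly 0.03 to 0.04.

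**5. Cross-check with other inputs.** Median-split allocation, N = 48, 20,000 runs for type I error and 8,000 for power. The implied r is √(1 − residual variance ratio).

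| Residual variance ratio | Implied r | Type I: own baseline → plus disability | Power at 0.8 SD: own baseline → plus disability |
|---|---|---|---|
| 0.996 | 0.06 | 0.049 → 0.049 | 0.871 → 0.868 |
| 0.967 | 0.18 | 0.049 → 0.052 | 0.878 → 0.880 |
| 0.937 | 0.25 | 0.044 → 0.049 | 0.876 → 0.894 |
| 0.797 | 0.45 | 0.038 → 0.051 | 0.818 → 0.875 |
| 0.778 | 0.47 | 0.035 → 0.049 | 0.891 → 0.942 |
| 0.571 (extreme) | 0.65 | 0.023 → 0.051 | 0.865 → 0.970 |

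The direction is the same. Near r = 0.5 the power gain here is 5 to 6 points, so 9 is towards the upper end. It depends on how much the outcome's own baseline already explains.

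**The case against.** The strongest reply is that nothing invalid happens. ANCOVA on the outcome's own baseline is unbiased here, and its error runs in the safe direction. The only powered comparison is RMQ, whose baseline is already in its model. The own baseline of pain or SF-36 may absorb most of what RMQ would predict, and where it does, power changes by 2 points or less. All of this stands, and it sets the severity.

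Three stronger readings are tempting, and the protocol does not support them.

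- **That the whole 2% / 5% / 15% from the limiting case is error in the standard error, or that r = 0.5 amounts to needing 33% more patients (1/(1 − 0.25) − 1).** The limiting case needs perfect balance, and the protocol states only that participants are balanced by degree of disability. Under stratification the overstatement is about 0–2% / 1–3% / 5–11%. The rest is the ordinary gain from any prognostic covariate, and nothing in the document supports a partial correlation as high as 0.5.
- **That every other outcome suffers.** Surface electromyography is a secondary objective and partly descriptive. The fear-avoidance, anxiety-depression and catastrophising scales serve in the objectives as influences on the treatment effect. A link between baseline RMQ and these, beyond their own baselines, is undocumented.
- **That false positives are inflated.** The error is in the opposite direction.

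It can also be said that the exact stratum term belongs in the analysis plan. That holds for its coding, but not for whether the factor is in the model, because the protocol already states the covariate for all tests.

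**Conclusion.** The mismatch is plain from the text: the factor that restricts allocation is missing from the fixed between-group models for pain and SF-36. Its consequence is small. For an assumed r of 0.2 to 0.3, type I error stays at about 0.042–0.049 and power loss is about 1 to 3 points. Only at r = 0.5 does it become noticeable, with type I error around 0.03 and a loss of up to about 9 points.

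These sizes assume 48 analysed patients, two or three allocation strata and a 0.8 SD effect. That disability is exempt assumes allocation used RMQ, the only activity-limitation scale named. If a different measure was used, the disability model may not carry the factor exactly either. Confidence is high in the textual mismatch and low in its size. This is a free improvement of minor severity.

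**What to change.** Reword the covariate sentence in Data collection and analysis along these lines: *each ANCOVA will adjust for the outcome's own pre-treatment value and for baseline disability (the RMQ score, or the category used for allocation)*. Apply it at least to the pain and SF-36 models. In the RMQ model the score is already present. State in the Intervention section which instrument and which categories were used for balancing, so that the term can be matched to the allocation.

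The cost is one degree of freedom if the score is used (residual 45 to 44 with 48 patients), or the number of categories minus one otherwise. No new data are needed, since the questionnaires are completed before treatment. The change should be made before unblinding, so that the added covariate cannot look data-driven. The sample size of 24 per group is unchanged, as it rests on RMQ.

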**Outcome measures**:

The following variables will be taken into account in the clinical trial:

- Sociodemographic data: age, sex, profession (classification according to CNAE), sedentary lifestyle (sedentary, sedentary with walking, light or intense physical effort), sporting activity (no sport, low-impact sport, high-impact sport; weekly frequency).

- Clinical variables: weight and height (BMI), process evolution time (in months), previous pharmacological treatment (type, dose, duration), previous physical treatment (type, duration), complementary examinations (Rx, CT, MRI)

- Evaluation of results:

Currently, there is consensus regarding the basic variables to be considered in the evaluation of results in the treatment of low back pain: pain, specific functional limitation due to low back pain, quality of life, work disability and satisfaction (22,23,24). Based on these consensuses, in the evaluation of results we will take into account the following variables:

- Pain intensity: Numerical Pain Scale (NPS), preferable to the visual analog scale because it is less abstract and easier to understand (24).
- Study of SEMG of lumbar spinal erectors, oblique / transverse abdominals, and hamstrings. The muscle activation pattern will be studied descriptively, checking the presence or absence of relaxation in maximum flexion. The pre and post-treatment patterns will be compared again, checking the existence or not of relaxation, and using averages and ratios of electromyographic activity.

• Limitations of the activity: validated version in Spanish of the Roland-Morris Questionnaire (RMQ), useful in situations of mild and moderate disability, more typical of the population usually attended in the MFyRHB consultations (25,26,27,28).

• Quality of life: validated Spanish version of the SF-36 questionnaire (29).

• Work situation: active in their usual job, active in a restricted job, Temporary Disability, Permanent Disability, unemployed due to health problems, unemployed for other reasons, student, housewife, retired (22).

• Fear-avoidance beliefs: validated Spanish version of the Fear Avoidance Beliefs Questionnaire (FABQ) (30,31) that measures beliefs and attitudes regarding the potential effect of work and physical activity on pain.

• Anxiety and depression: validated Spanish version of the Hospital Anxiety and Depression subscale (HAD) questionnaire (32,33,34) with demonstrated utility in screening for the possible presence of anxiety and depression states.

• Ideas of Catastrophizing in the face of pain: validated Spanish version of the Pain Catastrophizing Scale (PCS), which comprises 3 dimensions: rumination, magnification and hopelessness in the face of pain (35,36).

• Comorbidities: Charlston Comorbidity Index (37).

• Co-interventions: Parallel treatments that the participants may receive (other physiotherapeutic, pharmacological treatments, disc, facet or epidural infiltrations, TENS, electrotherapy or surgery) will be recorded.

• Adverse effects: adverse effects that occur during treatment will be recorded.

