**METHODS**

**Design**

Randomized, double-blind clinical trial, with 2 arms (VNM, Vplacebo), 3 assessing times (pre-treatment, at the end of treatment and follow-up at 6 months) and intention-to-treat analysis.

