**Power and sample size**

The study has been planned to obtain a difference of 3 points in the Roland Morris questionnaire since these values have been recognized as clinically relevant (18,19). According to the results of a previous sample of patients with CMLBP obtained in our center, the mean disability measured by the RM questionnaire had a SD of 3.2. Considering an alpha value of 0.05 and beta of 0.9 for comparison of two-tailed means, the required sample size is 24 patients per group to detect changes in disability. Considering losses of 20%, the study sample is established in 62 patients (20).

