**Data collection and analysis**

Sociodemographic data and clinical variables will be collected by clinical interview and by accessing the electronic history of the patient. The questionnaires as well as the EMGs will be obtained before the treatment, at the end of the treatment and at 6 months. Both the participants and the outcome assessors will be unaware of the allocation to each of the treatment arms. Primary outcomes will be obtained by intention-to-treat analysis.

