**Applications / Relevance of the study**

CMLBP is a very frequent process with a great personal impact, on health spending and on society, being the first cause of sick leave in those under 45 years of age.Currently, there is no effective treatment for CMLBP, and new treatment strategies have to be found to improve outcomes. If the treatment designed in this project is effective, it could be applied in the ordinary clinical practice of our health area and be disseminated by the SNS to improve the treatment of patients with CMLBP.

On the other hand, the wide dissemination of the application of VNM in the area of physical therapy requires the performance of quality clinical trials that allow objectively justifying its use in different processes, including CMLBP. At present, most of the rehabilitation treatments for low back pain are being applied without solid evidence to justify their use (38).

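### Adverse effects are recorded only during the 4-week treatment period, although both arms are assessed for benefit up to 6 months

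*Protocol*

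**What the plan says.** The last item in the protocol's list of outcome measures states that "adverse effects that occur during treatment will be recorded". No other sentence in the protocol deals with collecting harms.

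The Intervention section defines the treatment period: "The duration of treatment will be 4 weeks, changing the bandage 4 times, weekly". The Design section sets "3 assessing times (pre-treatment, at the end of treatment and follow-up at 6 months" for both arms. The Data collection and analysis section says what is gathered at those times: "The questionnaires as well as the EMGs will be obtained before the treatment, at the end of the treatment and at 6 months". Adverse effects are not mentioned there.

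The list of outcome measures also includes "Co-interventions: Parallel treatments that the participants may receive". That item covers infiltrations and surgery among others and carries no stated time limit.

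The main objective covers the short and the medium term, and the second hypothesis is that the effect persists at 6 months. The section on relevance ties a positive result to use: "If the treatment designed in this project is effective, it could be applied in the ordinary clinical practice of our health area".

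**The concern.** The trial looks for benefit over about half a year but looks for adverse effects, as such, only in the first 4 weeks. A site that follows the rule exactly would have no reason to record a reaction or flare that begins after the treatment period. It would also have no prompt to ask about one when the patient comes back at 6 months.

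This is a data-collection rule, so it belongs in the protocol and cannot be repaired later: an event that was never recorded cannot be recovered by any analysis plan. The trial hopes to support routine use on the strength of medium-term results. Its statement about harms would then cover a shorter period than its statement about benefit, and a reader of the results might not notice.

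**Working it through.** The plan gives no figure on this point to reproduce, so the check is mainly a comparison of its sections.

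**1. Window for harms.** It opens and closes with treatment (Outcome measures), and treatment is 4 weeks (Intervention).

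**2. Window for benefit.** There are three assessments, the last at 6 months, in both arms (Design; Data collection and analysis).

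**3. Content of the 6-month visit.** Questionnaires and electromyography. No section extends adverse-effect recording to this visit.

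**4. Length of the gap.** The protocol does not say whether 6 months runs from baseline or from the end of treatment. Taking 6 months as about 26 weeks (an assumption):

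- from baseline: 4 / 26 = 15.4% of follow-up lies inside the recording window, and 22 / 26 = 84.6% lies outside;
- from end of treatment: follow-up is 4 + 26 = 30 weeks, so 4 / 30 = 13.3% lies inside and 26 / 30 = 86.7% outside.

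These are shares of calendar time only. Exposure stops at 4 weeks, and nothing in the protocol suggests that risk is spread evenly over the months that follow. The fractions therefore do not estimate how many events would be missed.

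**5. What other items would still pick up.**

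- Worsening of pain, disability or quality of life that is present on the day of the 6-month assessment: yes, through the Numerical Pain Scale, Roland-Morris and SF-36, although it is not labelled an adverse effect.
- Worsening that led to another treatment: the treatment is recorded as a co-intervention, but not the event that prompted it or its relation to the bandage.
- An event that starts after treatment and resolves before 6 months: not recorded as an adverse effect.
- An event unrelated to pain or function, such as a skin reaction, starting after treatment: not recorded as an adverse effect.

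**6. Effect on the rest of the design.** The sample size rests on Roland-Morris alone: "The study has been planned to obtain a difference of 3 points in the Roland Morris questionnaire". Its inputs (difference, SD, alpha, power, losses) include nothing about harms. Changing the recording window alters neither the sample size nor any efficacy analysis.

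**The case against.** The strongest reply is that recording adverse effects during exposure is a clear rule for an adhesive bandage worn for 4 weeks. It contradicts no other section, safety is not among the stated objectives, and no figure in the protocol shows that delayed harm occurs. Reports gathered at 6 months will depend on memory and, in people with chronic low back pain, will include many events that have nothing to do with the bandage. All of this stands. It limits the weight of the point, but it does not explain why an existing visit should pass without the question.

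Two stronger readings are tempting, and the documents do not support them.

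- A reader might infer that all harm after treatment goes uncounted. That is too much: lasting deterioration is measured in both arms at 6 months, and co-interventions are recorded without a stated end date.
- A reader might infer that nothing is observed once the last bandage comes off. The protocol does not establish this. It schedules an end-of-treatment assessment and does not say whether the last removal comes before or after it.

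Nor can one say that the analysis would conceal the frequency of harms. The Data collection and analysis section already provides for categorical variables to be given as counts and percentages with 95% confidence intervals, so the rate in each arm would be visible for whatever was recorded. The gap lies in what is collected, not in how it is summarised.

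**Conclusion.** The point holds in a limited form. The protocol's one rule on harms confines recording to the 4-week treatment period, and no section asks about adverse effects at 6 months. Adverse effects with later onset would not be recorded as such. The loss falls mainly on transient events, or events unrelated to pain, that have resolved by the 6-month visit.

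The likely impact is small. Between 85% and 87% of follow-up time lies outside the window, on the assumption that 6 months is about 26 weeks, but the protocol gives no basis for turning that into a number of missed events. The conclusion rests on the plain reading of the rule and on the absence of any other text about collecting harms. It calls for an inexpensive improvement to the protocol and does not threaten the efficacy result.

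**What to change.** Amend the adverse-effects item under Outcome measures so that it states:

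- recording starts with the first bandage and continues through the end-of-treatment assessment, including any reaction after the last removal;
- adverse effects are asked about again at the existing 6-month visit, with the same question in both arms;
- events with onset during treatment and events with onset afterwards are reported separately, by arm, with 95% confidence intervals.

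Add adverse effects to the list of what is gathered at the visits in Data collection and analysis, so that the two sections agree.

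The cost is a short protocol change and one further question at a visit already planned, with no new visit and no change in sample size. The downside is that later events will rest partly on recall and will include unrelated background events. Separating them by time of onset and comparing them between arms helps the reader weigh this, but does not remove it.
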